#### **P. Plan for addressing confounding**

In the EHR cohort study period apixaban was a newly available treatment for the indication of interest leading to the possibility of channelling bias. The analysis cohort in this study is derived from observational data meaning there is likely to be confounding. To handle confounding for all objectives the treatment arms will be matched using the optimal method selected, for example by propensity score matching or coarsened exact matching. For objective 1 by applying the trial inclusion and exclusion criteria to both treatment cohorts and matching using the baseline covariates we should avoid channelling bias. It is possible that unmeasured or unknown confounding may remain and this will be explored and discussed in the analysis of the results.

[figure not shown]

#### **Q. Plans for addressing missing data**

##### **Missing Baseline Data**

UK EHR data have been shown to be almost complete for drug prescribing and information on important comorbidity are well recorded. The following variables used for matching may have missing data: weight and BMI, baseline systolic blood pressure, renal function, smoking status, and alcohol intake. Smoking increases the risk of stroke; we therefore anticipate that AF patients are likely to have been asked about their smoking status by their GP. A study comparing performance of ATRIA, CHADS2, and CHA2DS2-VASc risk scores in predicting stroke in patients with AF using CPRD data linked with HES found 6% of patients had smoking status not recorded. Alcohol use can trigger AF symptoms so we also expect that hazardous alcohol intake will be recorded in some cases. Where there are missing data on the baseline characteristics used for matching different approaches will be taken depending on the variable in question. In some cases, such as for renal function and alcohol intake, a patient is more likely to have no data entered if there is no overt clinical evidence of abnormality; in such cases we may take a pragmatic approach and use a simplified version of the variable such as categorising into a binary parameter (“evidence of high alcohol” vs “no evidence of high alcohol intake”) with those with no data included in the “no evidence of” groups. For BMI and SBP we cannot assume the data are missing at random as we expect that a patient is less likely to be weighed if they appear to be of healthy weight and is less likely to have blood pressure recorded if they do not have hypertension. Patients with missing BMI or SBP will therefore be excluded from the trial-eligible cohort. The number and proportion of patients with missing data for baseline variables will be summarised and the methods used to deal with the missing data described.

##### **Missing Prescription Data**

Treatment may be initiated in secondary care meaning the first prescription of patients newly initiating treatment is missing. To account for these potentially missing first prescriptions we will perform a sensitivity analysis where those newly initiating treatment are assumed to have a missing earlier prescription and therefore assigned an earlier derived index date. Patients who are hospitalised may also have prescriptions issued in secondary care leading to treatment gaps seen in their primary care prescription data. The primary analysis using the Prescribed Population will not be affected by such gaps as patient time is included until the patient is censored or experiences an event regardless of treatment gaps. The supplementary analysis using the On-treatment Population and the safety analysis censor at derived date of last dose and may therefore miss events whilst a patient was on treatment in hospital. We will investigate the occurrence of hospitalisation around treatment discontinuation and assess the potential impact on the results of such missed events by performing a sensitivity analysis with different extended derived dates of last dose (extending the final period to 60 or 90 days after the final prescription estimated end).

##### **Missing Outcome Data**

The problem of missing data on the outcome events will be addressed by performing a sensitivity analysis repeating the primary analysis on the ONS and HES-linked cohort. The linked cohort will be assembled by restricting the trial-eligible cohort to the patients with ONS-linked and HES-linked data prior to matching. Occurrence of events and detail of events (such as type of stroke) is expected to be better recorded in the linked cohort.

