**K. Planned use of linked data (if applicable):**

We intend to use CPRD data linked with HES in patient data to enable optimal stroke, MI, and major bleeding ascertainment, and ONS mortality data to determine deaths. When matching CPRD patients we plan to include the practice level deprivation level index as a matching variable because socioeconomic status is predicted to influence the likelihood of the primary study outcome of stroke.

[figure not shown]

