## L. Definition of the Study population

For all objectives two datasets of UK primary care data will be combined: CPRD Gold and CPRD Aurum. Patients with a prescription for an oral anticoagulant in the time period 01 January 2013 to 31 January 2019 (exact cut-off date dependent on date of final data extracts) and a prior diagnosis of atrial fibrillation will be selected as the EHR cohort. Apixaban gained UK marketing authorisation in January 2013 for the indication of prevention of stroke and systemic embolism in AF patients; the minimum date is set to capture all patients prescribed apixaban for this indication in the UK. A previous study validated the use of diagnostic read codes for identifying patients with AF in CPRD by sending surveys to GPs and found a confirmation rate of 98% among patients originally identified with AF codes.

### Objective 1

**Step 1:** We will select all (HES and ONS linked) patients in the EHR cohort who would have met the following eligibility criteria for inclusion in the ARISTOTLE study, at least 6 months after patient registration in an up to standard practice: or 6 months post-UTS date, whichever is later:

- a diagnosis of AF,
- age over 18 years,
- at least one of the following risk factors for stroke: diagnosis of congestive heart failure, hypertension requiring pharmacological treatment, age greater than 75, diabetes mellitus, and prior stroke or systemic embolism,
- no AF due to reversible causes (e.g. thyrotoxicosis, pericarditis),
- no clinically significant (moderate or severe) mitral stenosis, in EHRs clinical significance and severity are not consistently recorded therefore a diagnosis of mitral stenosis will be sufficient to exclude a patient,
- no increased bleeding risk that is believed to be a contraindication to oral anticoagulation (e.g. previous intracranial haemorrhage),
- no conditions other than AF that require chronic anticoagulation (e.g. prosthetic mechanical heart valve),
- no persistent, uncontrolled hypertension (systolic BP > 180 mm Hg, or diastolic BP > 100 mm Hg), in EHRs this will be implemented by excluding patients whose latest blood pressure reading in the 6 months prior to the index date is over the systolic or diastolic blood pressure limit
- no active infective endocarditis,
- no concomitant treatment with aspirin > 165 mg/day,
- no simultaneous treatment with both aspirin and a thienopyridine (e.g., clopidogrel, ticlopidine),

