- no severe comorbid condition with life expectancy of  $\leq 1$  year,
- no active alcohol or drug abuse, or significant psychosocial difficulties (e.g., psychosis, dementia),
- no recent ischemic stroke (within 7 days),
- no severe renal insufficiency (serum creatinine > 2.5 mg/dL or a calculated creatinine clearance < 25 mL/min),
- no ALT or AST > 2X ULN or a Total Bilirubin  $\geq 1.5$ X ULN (unless an alternative causative factor such as Gilbert's syndrome is identified),
- no platelet count  $\leq 100,000/\text{mm}^3$ ,
- no haemoglobin < 9 g/dL,
- no prior exposure to apixaban,
- no women who are pregnant or breastfeeding

For the 3 criteria involving patient laboratory results (renal insufficiency, low platelet count, and low haemoglobin) a patient will be excluded if their last test result in the 90 days prior to the index date meets the exclusion criteria.

**Step 2:** Next we will determine if/when these patients received apixaban or warfarin. Individuals in EHR who have more than one warfarin eligibility period within their record will be able to contribute more than once to the pool of warfarin subjects (with the covariates and person-time contributed unique to the specific eligibility period) as long as they have no past apixaban exposure.

**Step 3:** Having obtained individual level patient data for ARISTOTLE participants from Bristol Myers-Squibb we will then match each ARISTOTLE apixaban participant 1:1 with the closest available apixaban patient record in our EHR pool. We will consider matching on a selection of the following ARISTOTLE baseline characteristics:

- age
- sex
- body mass index
- systolic blood pressure (mmHg)
- history of congestive heart failure or left ventricular systolic dysfunction

[figure not shown]

- hypertension requiring pharmacological treatment
- diabetes mellitus
- prior stroke or TIA or thromboembolism
- smoking status [current smoker, former smoker, or never smoked]
- alcohol consumption [none, low, moderate, heavy]
- renal impairment [severe, moderate, mild, normal based on the CrCL value]
- prior VKA/warfarin use
- concomitant treatment with:
  - anticoagulant/VKA use other than warfarin or apixaban
  - aspirin
  - antiplatelets
  - NSAIDs
  - lipid lowering drug therapy
  - CYP3A4 inhibitors

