We anticipate matching all or the majority of ARISTOTLE apixaban subjects with an EHR patient, giving us a pool of ARISTOTLE-analogous apixaban patients, with similar baseline characteristics as ARISTOTLE subjects at the point of randomisation (n~9,000).

The variables selected as potential matching variables are those known or suspected to influence the likelihood of the outcomes of interest. The exact selection of matching variables will depend on the quality and completeness of the data available and a balance will be struck between the matched sample size and sample balance. Variables may be grouped together to increase the sample size, for example by grouping concomitant medications that increase bleeding risk. Continuous variables may be coarsened by splitting into appropriate categories. A procedure will be employed to facilitate selection of a matched cohort, for example via coarsened exact matching for example by use of the %CEM SAS macro. Coarsened Exact Matching is a nonparametric matching method that has been found to give estimates of casual effects with lower variance and bias for a given sample size compared with other commonly used methods of matching.

Figure 1: Assembly of Matched Trial-analogous Cohort of EHR Patients

[figure not shown]

Step 4: The resulting trial matched sample of EHR apixaban exposed subjects will be matched to the warfarin ARISTOTLE-eligible EHR subjects (Figure 1) using a matching method such as propensity score matching (PSM), or CEM (with the final method selected based upon method giving the optimal sample size versus balance). Where an individual from EHR has multiple warfarin “eligibility periods” that can be matched to an apixaban trial matched subject, the EHR characteristics that will be matched on will be those from the beginning of the specific eligibility period. The covariates for consideration in the matching between EHR treatment arms or construction of a PS model will include the variables listed above used in in step 3 along with additional EHR variables such as data source (CPRD Gold or Aurum), socioeconomic status, and comorbidities. The hazard ratio for the outcomes of interest (listed in section N) will then be calculated. Each apixaban patient from the ARISTOTLE-eligible EHR

[figure not shown]

patients will be matched 1:1 with the warfarin EHR patient with the closest match giving a trial-analogous analysis cohort of ~18,000.

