#### **N. Exposures, Outcomes and Covariates**

The exposures of interest are apixaban, warfarin, rivaroxaban, and dabigatran (any dose for each exposure).

The individual effectiveness outcomes:

- stroke
- systemic embolism
- myocardial infarction
- all cause death

The safety outcome for the study:

- major bleeding (bleeding requiring transfusion, bleeding at a critical site, bleeding requiring attendance at hospital, or fatal bleeding)

For all outcomes we make the assumption that if there is no record of an outcome then the outcome did not occur.

The EHR ARISTOTLE-eligible patients prescribed apixaban will be matched to the ARISTOTLE apixaban patients on the variables listed in section L (step 3 of objective 1), with value taken at baseline (value at time of first dose or latest measurement/data recorded prior to first dose).

When matching between the treatment arms within the EHR cohort of patients the variables to be considered for inclusion in the matching algorithm include those listed in section L used in matching from the EHR treatment arm to the trial patient data in addition to EHR variables such as data source (CPRD Gold or Aurum), socioeconomic status, and comorbidities.

[figure not shown]

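### The planned check on missing outcomes does not measure missing outcomes: it either repeats the primary analysis or changes the patients along with the completeness of recording

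*Protocol*

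**What the plan says.** Section Q (Missing Outcome Data) deals with missing outcomes by one sensitivity analysis, "repeating the primary analysis on the ONS and HES-linked cohort". It fixes where the restriction falls: "The linked cohort will be assembled by restricting the trial-eligible cohort to the patients with ONS-linked and HES-linked data prior to matching". The reason given is that "Occurrence of events and detail of events (such as type of stroke) is expected to be better recorded in the linked cohort".

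Three other places bear on this.

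- Section L, Objective 1, Step 1 defines the primary cohort: "We will select all (HES and ONS linked) patients in the EHR cohort who would have met the following eligibility criteria".
- Section K plans linkage for outcomes in general, without confining it to a sensitivity analysis: "We intend to use CPRD data linked with HES in patient data to enable optimal stroke, MI, and major bleeding ascertainment". ONS data are planned for deaths.
- Section N assumes for all outcomes that "if there is no record of an outcome then the outcome did not occur".

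Both matching steps in Section L depend on the pool. Step 3 is to "match each ARISTOTLE apixaban participant 1:1 with the closest available apixaban patient record in our EHR pool". In Step 4 the apixaban "patients will be matched 1:1 with the warfarin EHR patient with the closest match giving a trial-analogous analysis cohort of ~18,000".

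**The concern.** An analysis aimed at missing outcomes should vary outcome capture and hold everything else still. Section Q varies the eligible pool instead. Whether that changes anything depends on a fact on which the protocol gives two accounts: whether the primary cohort already consists of linked patients only.

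The stake is the Objective 1 validation. Section O requires the hazard ratio for stroke or systemic embolism to lie between 0.69 and 0.99, and Section N treats an unrecorded event as no event. If capture differs between arms, the hazard ratio moves, and it could move towards or across a limit of that window. Section Q is the one analysis directed at this, and no section compares outcome sources within the same patients.

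**Working it through.** **Reading 1: the primary cohort is linked (Sections L and K as written).** The trial-eligible cohort that Section Q restricts is the cohort that Step 1 of Section L has already limited to linked patients. The restriction removes nobody, the matching pool is the same, and the outcome sources are the same. The result reproduces the primary hazard ratio and carries no information on missing outcomes.

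**Reading 2: the primary cohort includes unlinked patients (implied by Section Q).** The restriction precedes both matching steps, and each step takes the closest record in the pool. A smaller pool can therefore alter:

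1. who is in the cohort;
2. which EHR patient stands for which ARISTOTLE participant;
3. which warfarin patient is paired with which apixaban patient;
4. how completely outcomes are recorded.

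Only the fourth is the target.

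**Pool size.** Section J's figures reproduce: 23,526 × 0.60 = 14,115.6 (stated 14,115), and 14,115.6 + 8,407 (Section I) = 22,523 (stated as more than 22,000). Section J shows no reduction for linkage. With an assumed linked share of 60%, 70% or 80%, the apixaban pool is about 13,514, 15,766 or 18,018. It falls below the protocol's own minimum of 15,000 when the share is under 15,000 / 22,523 = 66.6%.

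**How far a change of patients alone could move the result.** Precision is borrowed from the ARISTOTLE interval quoted in Section O (0.66 to 0.95):

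SE(log HR) = (ln 0.95 − ln 0.66) / 3.92 = 0.093.

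For two matched cohorts of equal size sharing a fraction f of their information, the SE of the difference in log HR is 0.093 × √(2(1 − f)). The 95% chance range for the ratio of the two hazard ratios is exp(±1.96 × SE):

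| Assumed overlap f | SE of difference | Ratio of HRs |
|---|---|---|
| 0.50 | 0.093 | 0.83 to 1.20 |
| 0.75 | 0.066 | 0.88 to 1.14 |
| 0.90 | 0.042 | 0.92 to 1.09 |
| 1.00 | 0 | 1.00 |

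A cruder version treats the linked cohort as a subset of unchanged pairs making up a fraction L of the whole. The SE is then 0.093 × √(1/L − 1), which gives 0.86 to 1.16 at L = 0.6 and 0.91 to 1.10 at L = 0.8. That is not the planned design, but the size is similar.

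**How large the signal might be.** With uncommon events, observed HR ≈ true HR × (capture in apixaban / capture in warfarin). The capture figures are assumptions.

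- 75% against 80%: 0.79 × 0.75/0.80 = 0.74, a ratio of 0.94.
- 80% against 75%: 0.79 × 0.80/0.75 = 0.84, a ratio of 1.07.
- 70% against 80%: 0.79 × 0.70/0.80 = 0.691, next to the lower limit of 0.69.

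The first two shifts lie inside the chance range at every overlap shown up to 0.90.

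**With patients and pairs fixed**, f = 1. The part of the shift that comes from a change of patients is zero, and what remains comes from the outcome source.

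**The case against.** The strongest reply is that Section Q claims little. It repeats the primary analysis where recording should be better, and it sets no rule for attributing a difference to missing data. Restricting before matching is also sound practice: it keeps pairs and balance intact, whereas dropping unlinked patients after 1:1 matching breaks every pair with one unlinked member. If linkage were independent within pairs (an assumption), only 36% to 64% of pairs would survive at 60% to 80% linked. Both points stand. The re-matched estimate is valid in its own right and should not be discarded. It still does not answer the question under whose heading it is placed.

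Four stronger readings are tempting, and the protocol does not support them.

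- *The sensitivity analysis certainly re-selects and re-matches patients.* Section L's wording points the other way, so this holds only on Reading 2.
- *The outcome source is switched.* Nothing says that a linked patient's events come from GP records in the primary analysis and from HES and ONS in the sensitivity analysis. Section K suggests linked sources throughout, in which case completeness changes only through who is included.
- *Unchanged hazard ratios would hide a loss of events that is equal in both arms, and so undermine Objective 1.* Such a loss lowers absolute rates and precision but leaves the hazard ratio essentially unbiased, and the Section O criteria concern the hazard ratio and its upper confidence limit.
- *Objective 1 fails with this check.* Its conclusion rests on the Section O criteria applied to the primary analysis.

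Section T does plan to compare event rates between Gold and Aurum. That contrasts two databases; it does not show how many events either one misses.

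**Conclusion.** The point holds on both readings, for different reasons. As Sections L and K stand, the check is a duplicate. If unlinked patients are in the primary cohort, the check mixes a change of patients and pairs with a change in completeness. A shift of roughly 10 to 20% in the hazard ratio could then arise from the change of patients alone. That size is illustrative. It rests on ARISTOTLE-like precision and an assumed overlap or linked share, neither of which the protocol gives for this analysis, and at 90% overlap it is a little under 10%. The contradiction between Sections L and Q needs no assumption. The consequence is limited to the interpretation of one sensitivity analysis, but it is the one directed at the Section N assumption, and a better comparison is available from data already requested.

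**What to change.** 1. Reconcile Sections L and Q. State whether the primary Objective 1 cohort is restricted to HES- and ONS-linked patients, and which sources define its outcomes.
2. If it is not restricted, keep the linked, re-matched analysis as a supportive estimate in better-recorded patients.
3. Add a comparison within that one linked matched cohort, or within the primary cohort if it is already linked, holding patients and pairs fixed. Run the primary Cox model with GP-recorded outcomes only, then with GP plus HES plus ONS outcomes. Tabulate by arm and stroke type the events found in GP records only, in HES or ONS only, and in both. Use the ratio of the two hazard ratios and the arm-specific capture fractions as the measure of missing outcomes.

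Forming the cohort by restricting before matching avoids the broken pairs described above. The cost is protocol wording and a little more analysis; HES Admitted Patient Care and ONS death data are already requested in item 13. The result describes linked patients only, and it cannot count events that no source recorded.

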#### **R. Patient or user group involvement (if applicable)**

Patients have not been involved in the setting of this study question. However we will consult with patient groups and relevant charities in communicating the findings of the study.

#### **S. Plans for disseminating and communicating study results, including the presence or absence of any restrictions on the extent and timing of publication**

The study protocol will be submitted for publication in BMJ Open. The results of the study will be submitted to peer reviewed journals and will be presented at conferences such as the International Society of Pharmacoepidemiology conference. Results will also be published on the London School of Hygiene and Tropical Medicine website and in the PhD thesis of the principal investigator. Results that may impact on treatment guidelines will be shared with policy makers such as the Medicines and Healthcare products Regulatory Agency and the National Institute for Health and Care Excellence.

##### **Conflict of interest statement:**

The principal investigator (PI) is funded by a UK Medical Research Council PhD studentship.

[figure not shown]

#### **T. Limitations of the study design, data sources, and analytic methods**

Some of the criteria that should be assessed for ARISTOTLE eligibility may not be well recorded in CPRD. Criteria such as “increased bleeding risk” are vague and it is not clear exactly which Read codes should be included and time scale considered. Other criteria such as alcohol and drug abuse may not be captured for all patients in CPRD. These limitations are consistent with our aim to select a population as similar as possible to the ARISTOTLE trial population with the acknowledgment that differences will remain. The most important risk factors for the primary outcome of stroke (the components of the CHA2DS2-VASc score for AF stroke risk of age, sex, history of congestive heart failure, hypertension, stroke/TIA history, vascular disease history, and diabetes) are mostly well recorded in CPRD.

There are differences in the coding systems used by the two datasets and it is possible that the completeness of coding differs between the two. The potential impact of the different coding systems and completeness of coding will be ascertained by comparisons of the rates of diagnoses, events, baseline variables (such as smoking status, alcohol use, lab values, and vital signs), and prescriptions of interest. Including the data source (Gold or Aurum) as one of the matching variables should prevent discrepancy between the two datasets from biasing the results.

The main focus of the study is the validation of our methodology through assembling a cohort of patients comparable to the patients included in ARISTOTLE and finding similar results to the trial. Criteria to determine the success of the methodology have been pre-specified in the protocol. Given the use of CPRD data to determine treatment effectiveness is not yet well established, a finding that these data are not suitable to answer questions on intended effectiveness will be a useful conclusion.

